## Glossary / abbreviations

|            |                                                                                                                                                                                                                      |
|------------|----------------------------------------------------------------------------------------------------------------------------------------------------------------------------------------------------------------------|
| ACS        | Acute coronary syndrome                                                                                                                                                                                              |
| AE         | Adverse event - any undesirable event in a subject receiving treatment according to the protocol, including occurrences which are not necessarily caused by or related to administration of the research procedures. |
| AR         | Adverse reaction – any undesirable experience that has happened a subject while taking a drug that is suspected to be caused by the drug or drugs                                                                    |
| BHI        | Bristol Heart Institute                                                                                                                                                                                              |
| BRI        | Bristol Royal Infirmary                                                                                                                                                                                              |
| BRU        | Biomedical Research Unit                                                                                                                                                                                             |
| CABG       | Coronary artery bypass grafting                                                                                                                                                                                      |
| CAD        | Coronary artery disease                                                                                                                                                                                              |
| CMR        | Cardiac magnetic resonance                                                                                                                                                                                           |
| CRB        | Cardiovascular research board                                                                                                                                                                                        |
| CRF        | Case report form                                                                                                                                                                                                     |
| CTEU       | Clinical Trials and Evaluation Unit                                                                                                                                                                                  |
| DMSC       | Data monitoring and safety committee                                                                                                                                                                                 |
| ECG        | Graphical representation of electrical activity of the heart over time, as recorded by an electrocardiograph                                                                                                         |
| eGFR       | Estimated glomerular filtration rate: derived from gender, age, ethnicity and serum creatinine                                                                                                                       |
| IMR        | Index of microcirculatory resistance                                                                                                                                                                                 |
| IS         | Infarct size                                                                                                                                                                                                         |
| LV         | Left ventricle                                                                                                                                                                                                       |
| MACE       | Major cardiac adverse event                                                                                                                                                                                          |
| MI         | Myocardial infarction                                                                                                                                                                                                |
| MVO        | Microvascular resistance                                                                                                                                                                                             |
| NIHR       | National Institute for Health Research                                                                                                                                                                               |
| PCI        | Percutaneous coronary intervention                                                                                                                                                                                   |
| PPCI       | Primary percutaneous intervention                                                                                                                                                                                    |
| PIL        | Patient information leaflet                                                                                                                                                                                          |
| REC        | Research ethics committee                                                                                                                                                                                            |
| SAE        | Serious adverse event - events which result in death, are life threatening, require hospitalisation or prolongation of hospitalisation, result in persistent or significant disability or incapacity.                |
| SAR        | Serious adverse reaction                                                                                                                                                                                             |
| SOP        | Standard operating procedure                                                                                                                                                                                         |
| SSAR       | Suspected serious adverse reaction                                                                                                                                                                                   |
| STEMI      | ST segment elevation myocardial infarction                                                                                                                                                                           |
| SUSAR      | Suspected unexpected serious adverse reaction - an untoward medical occurrence suspected to be related to a medicinal product that is not consistent with the applicable product information and is serious.         |
| TMG        | Trial management group                                                                                                                                                                                               |
| TSC        | Trial steering committee                                                                                                                                                                                             |
| UH Bristol | University Hospitals Bristol NHS Foundation Trust                                                                                                                                                                    |

## 1. Trial summary

This is a single centre study in heart attack patients. This study investigates the relationship between the narrowing in small heart artery vessels as measured by a technique called the index of microcirculatory resistance and the effects of this narrowing as measured on cardiac magnetic resonance imaging.

## 2. Background

### Summary for the Non-Expert

- Coronary heart disease (CHD) is a leading cause of death in the UK. During a heart attack (myocardial infarction) a blockage in a coronary artery prevents the flow of oxygen and nutrients to the territory of the heart muscle supplied by this artery resulting in damage to the heart. Some of this damage is reversible, some irreversible. Following a heart attack, the extent of the damaged heart muscle increases the risk of developing chronic heart failure.
- The treatment for a heart attack is two-fold: 1) medication to inhibit clot formation and reduce risks of further coronary events and medication to prevent the development of heart failure in the longer term; and 2) mechanical stabilisation of the culprit lesion in the coronary artery with percutaneous coronary intervention (PCI) and intracoronary stent deployment.
- Patients suffering heart attacks present a variety of different heart attacks size and characteristics as assessed by cardiovascular MRI. The determinants for these variable phenotypes are not complete clear and explored.
- Despite a successful PCI, a significant amount of damage still occurs to the heart muscle. This research proposal investigates the association between the degree of microvascular resistance using the index of microvascular dysfunction (IMR), and the myocardial infarct characteristics on cardiac magnetic resonance imaging (CMR). By quantitating the association between IMR and the myocardial infarct characteristics on cardiac magnetic resonance imaging, this study aims to develop clinical endpoints that can be used to assess the benefit of future strategies to minimise ischaemia/ reperfusion injury and thus to minimise damage caused by a myocardial infarction.
- Patients with heart attacks will be recruited via the Bristol Heart Institute.
- The multidisciplinary team has the required skills and experience for undertaking this clinical study and will include: cardiac MRI and Interventional cardiologists, cardiac biology specialists clinical Trials Unit expertise (Clinical Trials Manager, Statisticians, Database manager). The costs of the study will be for staffing, IMR catheters, cardiac MRI scans and clinical trial unit costs. There will be no costs to the NHS.

### **RATIONALE FOR CURRENT STUDY**

Coronary heart disease (CHD) causes over 90,000 deaths a year in the UK: approximately one in five deaths in men and one in six deaths in women. Death rates from CHD in the UK are still amongst the highest in Western Europe. CHD is not only the single most common cause of death in the UK; it is also very costly, imposing a huge annual burden on UK economy. Despite continued advancement in treatment strategies for myocardial infarctions, the morbidity and mortality of patients presenting with myocardial infarction remains significant.

Novel insights into the microcirculatory effects of a myocardial infarction and infarct characteristics may offer new strategies to tailor therapy to improve health outcomes. By quantitating the association between IMR and the myocardial infarct characteristics on cardiac magnetic resonance imaging, this study aims to develop clinical endpoints that can be used to assess the benefit of future strategies to minimise ischaemia/ reperfusion injury and thus to minimise damage caused by a myocardial infarction. This study will also identify the patients at a higher risk following STEMI who would benefit the most from early adjuvant therapies as they become available.

Despite aggressive strategies to restore coronary blood flow quickly in an acute myocardial infarction with PPCI, cardiomyocyte necrosis still occurs and an associated mortality persists. This injury is in part due to cell death after flow restoration; the result of a biochemical signalling cascade known as ischaemia/reperfusion (IR) injury. Mechanical opening of the culprit artery does not always ensure good blood flow distal to the lesion; a condition referred to as “no reflow” which is associated with an increased mortality. This is multifactorial and poorly understood but the distal microcirculation is believed to be key to this phenomenon.

The index of microcirculatory resistance (IMR) can be measured using a using thermodilution pressure catheter. The fractional flow reserve (FFR), the coronary flow reserve (CFR) and IMR can be measured simultaneously. The feasibility and reliability of thermodilution-derived CFR has previously been established. The IMR specifically assesses the microvascular disease. IMR has been validated in animal and human studies and these studies have demonstrated that IMR measurement is largely independent of variations in hemodynamic state and therefore superior to FFR and CFR as it is not impacted by stenosis in the epicardial vessel.

[figure not shown]

Proof of concept studies for Doppler flow measurements in acute myocardial infarction have previously been carried out. Microcirculatory dysfunction has been shown to be associated

with reperfusion syndrome following acute myocardial infarction and poor ST segment resolution on ECG. Following myocardial infarction, the IMR predicts infarct size as measured by creatinine kinase rise and wall motion abnormalities as measured on echocardiography. The degree of microcirculatory dysfunction following STEMI as measured by the index of microcirculatory resistance (IMR) is correlated with both infarct size as measured by troponin, presence or absence of MVO on CMR and can predict LV function on transthoracic echocardiogram following STEMI.

CMR has become the gold standard for surrogate endpoints in clinical trials. CMR of myocardial infarction has been correlated with histology. It can accurately measure infarct size, LV volumes, myocardial salvage, microvascular obstruction (MVO) and myocardial oedema. Myocardial infarct size, myocardial salvage and MVO have all been shown to be associated with worse outcomes. CMR studies have shown that MVO is associated with larger infarct size and a worse prognosis.

Circulating micro-RNA have recently been identified as novel biomarkers in cardiovascular disease. Levels of circulating micro-RNA are increased in acute coronary syndromes and myocardial infarction. Circulating micro-RNA have been validated against troponin levels and may provide insight into the cause of ischaemia/ reperfusion injury and consequently the no reflow phenomenon.

All the factors that lead to a large myocardial infarction, and consequently a worse outcome, are not known. This study aims to identify myocardial infarctions that are associated with microcirculatory dysfunction and the CMR infarct characteristic of poor prognosis. By quantitating the association between IMR and the myocardial infarct characteristics on cardiac magnetic resonance imaging, we aim to validate this technique to risk stratify patients with myocardial infarction and therefore identify patients who would benefit from future interventional treatments to minimize damage caused by a myocardial infarction.

A search of registry databases suggests there are no ongoing studies examining the associations between the index of microcirculatory resistance and infarct characteristics on CMR.

### **3. Aims and objectives**

Aims:

To quantitate the association between IMR and MI phenotype.

To investigate the association between biomarkers and IMR with known CMR characteristics of poor outcomes.

Research Question:

In ST segment elevation myocardial infarction (STEMI) patients undergoing primary percutaneous coronary intervention (PPCI), does the degree of microcirculatory dysfunction assessed by the index of microcirculatory dysfunction (IMR) predict the phenotype of myocardial infarction as evaluated by cardiac magnetic resonance (CMR)?

## 4. Plan of Investigation

### 4.1 Trial schema

[figure not shown]

**Figure 1** Trial schema

### 4.2 Trial design

Single centre study investigating the association between infarct characteristics and microcirculatory dysfunction based at the Bristol Heart Institute. Microcirculatory dysfunction will be assessed using the index of microcirculatory resistance (IMR). Data collection and analysis will be undertaken in the Bristol Heart Institute NIHR BRU.

### 4.3 Trial population

#### • Study population:

Male and female patients (>18 years old) presenting with a suspected STEMI (ST-elevation on electrocardiogram) within 12 hours of chest pain. No coronary collaterals and TIMI flow <1.

• **Planned interventions:**

**STEMI patients intervention as part of clinical care:** On arrival to hospital, emergency patients with STEMI will be taken directly to the cardiac catheterisation for primary PCI. This is time critical with national targets of door to balloon time of 60 mins. Standard primary PCI treatment includes thromboaspiration and restoration of flow with stent deployment.

**STEMI patients additional measurement as part of research study:** Following completion of standard treatment of the heart attack, the IMR measurement will be performed; a pressure thermistor wire will be passed through the catheter already in situ for the PPCI. To achieve maximal hyperaemia for this measurement, an infusion of adenosine will be administered via a peripheral cannula. Verbal assent for inclusion in the study and this measurement will be performed on arrival in the catheter lab following the explanation of the PPCI. This is in accordance with previous and current studies in the department (Comfortable, Pinpoint, Erupt).

All acute coronary syndrome medical treatment will be unaffected. Consent for continued inclusion in the study will be performed at 24 hours.

At day 2-4 following myocardial infarction, baseline CMR will be undertaken. This will be repeated at 3 months. Blood samples for biomarkers will be taken at the time of angioplasty, at 24 hours and at the 3 months CMR follow up visit.

#### *4.3.1 Inclusion criteria*

Participant may enter study if ALL of the following apply

- >18 years old
- Cardiac symptoms of > 20 mins chest pain or equivalent.
- ECG criteria consistent with STEMI (STEMI)
- Proceeding with percutaneous angioplasty
- Assent/ consent to the study

#### *4.3.2 Exclusion criteria*

Participant may not enter study if ANY of the following apply

- Known allergy to adenosine or gadolinium
- Chronic atrial fibrillation
- Renal impairment with eGFR <30
- Contraindication to angiography
- Contraindication to CMR (implanted pacemaker/ defibrillator, ferromagnetic metal implant/ injury, claustrophobia, obesity/ too large for CMR scanner)
- Cardiogenic shock
- Patients with special communication needs or altered consciousness.
- Patients who do not give assent/consent to the study

#### **4.4 Primary and secondary outcomes**

#### 4.4.1 Primary outcome

Microvascular obstruction as a percentage of the left ventricle at 2-4 days.

#### 4.4.2 Secondary outcomes

**CMR outcomes:** Myocardial infarct size, microvascular obstruction, myocardial salvage, LV volumes, mass and ejection fraction at baseline and at 3 months follow up CMR.

**Biomarker outcomes:** micro-RNA and proteomics on admission, 24 hours and at follow up

**Angiographic outcomes:** TIMI score in the infarct related artery pre and post PPCI, myocardial blush grade following PPCI, BARI and APPROACH scores following PPCI, coronary collateral circulation (Rentrop classification)

**ECG:** ST segment resolution at 90 minutes following PPCI

#### 4.5 Sample size calculation

The sample size has been calculated for the primary analysis which will examine the association between MVO and IMR.

The study size has been set at 50 patients. A study of this size will have 80% power to detect a significant correlation between MVO at 2-4 days and IMR of 0.40 or more and 90% power to detect a correlation of 0.45 or more, at 5% statistical significance (2-sided). These values represent moderate correlations between the two measures. In a regression analysis, adjusted for three covariates, the study will also have 80% power to detect a difference in the model  $R^2$  of 0.1 between a model with just the three covariates (base model) and one with the three covariates plus IMR, assuming the base model  $R^2$  is at least 0.3. These values represent conservative estimates of the association between the variables. If the base model  $R^2$  is greater 0.3 then the power will increase and smaller changes will be detectable with 80% power. For example, if the base model  $R^2$  is assumed to be 0.7, a difference in model  $R^2$  of 0.05 could be detected with 80% power.

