# **6. Statistical analyses**

## **6.1 Plan of analysis**

Continuous data will be summarised using means and standard deviations (or median and interquartile range if the distribution is skewed). Category variables will be reported at a frequency and percentage. The association between the primary outcome, MVO at 2-4 days and IMR will be quantified using multiple linear regression, assuming the measures will be transformed (e.g. to a logarithmic scale) as necessary to induce normality. The analysis will be adjusted for three covariates – age, gender and time since MI. The relationship between the outcome and each predictor will be explored graphically and the model will be extended to include non-linear functions if non-linear relationships are indicated.

Secondary outcomes will also be analysed using multiple linear regression (continuous measures) or logistic regression (binary measures). Continuous outcomes measured at both 2-4 days and at 3 months will be modelled using a mixed regression model, which will account for the correlation between repeated measurements on the same individual. If a baseline value is also available this will be measured jointly with the subsequent measures.

Associations will be quantified and reported with 95% confidence intervals.

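### The 80% power stated in section 4.5 for an R² gain of 0.1 over a base R² of 0.3 is about 76% when IMR and the covariates are treated as observed, as they are in this cohort

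*Protocol*

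**What the plan says.** All the power statements are in protocol section 4.5, which presents the sample size as calculated for the primary analysis of MVO and IMR. "The study size has been set at 50 patients".

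- **Correlation:** "A study of this size will have 80% power to detect a significant correlation between MVO at 2-4 days and IMR of 0.40 or more". The same sentence gives 90% power for 0.45, at a two-sided 5% level.
- **Adjusted regression, main case:** "In a regression analysis, adjusted for three covariates, the study will also have 80% power to detect a difference in the model". The measure meant is R²: it is to rise by 0.1 when IMR joins the covariates, from a starting value of at least 0.3. The section adds that power rises if the base R² is higher.
- **Adjusted regression, second example:** at a base R² of 0.7, a difference of "0.05 could be detected with 80% power".

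Section 6.1 makes the adjusted model the primary analysis: "The analysis will be adjusted for three covariates – age, gender and time since MI". Section 5.11 describes a non-randomised study that enrols consecutive consenting patients. Section 4.5 names no formula or software, and does not say whether the predictors are treated as fixed or observed.

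**The concern.** The R² statements in section 4.5 are the ones that describe the model in section 6.1, so the 80% at base R² 0.3 is the power figure attached to the main test. The usual formula for an R² increment treats the predictor values as fixed by design. Here nobody sets IMR, age, gender or time since MI; they are whatever the enrolled patients have. The amount of information on IMR left after adjustment is then lower on average than that formula assumes, and it varies from sample to sample. Both effects reduce power. At stake is whether the plan states the right risk of missing an association at the smallest base R² it assumes.

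**Working it through.** **Inputs.** From section 4.5: n = 50, two-sided 5% (stated for the correlation and taken to apply to the regression), base R² = 0.3, gain = 0.1. From sections 4.5 and 6.1: three covariates plus IMR.

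**Derived quantities.**
- Full-model R² = 0.3 + 0.1 = 0.4.
- f² = 0.1 / (1 − 0.4) = 0.1667.
- Squared partial correlation = 0.1 / (1 − 0.3) = 0.1429, so the partial correlation is 0.378.
- The test of IMR has 1 numerator df and 50 − 5 = 45 error df.

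**Step 1: reproduce the stated figure.** With fixed predictors, the F statistic is noncentral F(1, 45) with λ = 50 × 0.1667 = 8.33. Power is **80.6%**, and the gain detectable at 80% is 0.0986. This matches the protocol's 80% and 0.1.

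**Step 2: treat the predictors as observed.** The intercept and three covariates use 4 of the 50 degrees of freedom in IMR. With IMR normal given the covariates, λ = f² × X, where X is chi-square with 50 − 4 = 46 df.
- Fixing λ at its mean, 46 × 0.1667 = 7.67, already lowers power to 77.3%.
- Averaging the noncentral F power over the distribution of X gives **76.0%**.
- A simulation of the planned test (200,000 runs, normal covariates correlated with IMR) also gives 76.0% (0.7605). With gender simulated as binary (100,000 runs) the result is 75.9%.

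**Step 3: what would give 80% with observed predictors.**

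| Change one input | Value needed |
|---|---|
| R² gain, at n = 50 and base 0.3 | about 0.109 |
| Base R², at n = 50 and gain 0.1 | about 0.36 |
| n, at base 0.3 and gain 0.1 | 55 (80.3%; n = 54 gives 79.5%) |

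**Step 4: the other statements in section 4.5.**

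| Statement | Fixed | Observed |
|---|---|---|
| Correlation 0.40, 80% claimed | 85.6% | 83.5% |
| Correlation 0.45, 90% claimed | 93.7% | 91.9% |
| Base R² 0.7, gain 0.05, 80% claimed | 87.2% | 82.8% |
| Base R² 0.3, gain 0.1, 80% claimed | 80.6% | **76.0%** |

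Only the last row falls below its claim. Read as partial correlations given the three covariates, 0.40 and 0.45 have 81.1% and 90.2% power with observed predictors.

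**The case against.** The strongest defence is that the fixed-predictor formula is a standard convention and reproduces the stated figure, so the protocol chose one accepted method over another. That stands: this is not an arithmetic error, and calling it one would be wrong. It does not settle which method suits the design. The convention describes power given a particular set of predictor values, whereas a cohort planned around R² values before any patient is enrolled needs power averaged over the samples it might draw.

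The defence can add that 76% is itself model-dependent. That also stands. If IMR stayed clearly skewed in the model (an assumed log-normal with sigma 0.6), simulation gives about 72%. But section 6.1 plans transformation towards normality, and this departure moves power further from 80%.

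It can also say that the gap is small and closes at a base R² of about 0.36. True, but section 4.5 makes its claim from 0.3 upwards, and at 0.3 it is not met.

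A reader might go further and infer that section 4.5 contradicts itself. The documents do not support this, in either of two forms:
- A gain of 0.1 over 0.3 is a partial correlation of 0.378, below the 0.40 given for 80% power. But 0.40 is a rounded-up value, not a sharp limit. Under the fixed-predictor method an unadjusted 0.378 gives 80.7%, in line with 80.6% for the adjusted test. A conflict appears only if one sentence is computed by one method and the next by the other.
- The two R² examples are both labelled 80% but differ by about 7 points under a single method. The second is conservative rounding: its fixed-predictor limit is a gain of 0.042, stated as 0.05. A claim of 80% where the power is higher is not false.

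**Conclusion.** The concern holds as a modest overstatement. For the primary adjusted test, at the minimum base R² that the protocol assumes, power is about 76% rather than 80%, so the false-negative risk is about 24% rather than 20%. The cause is a convention that does not match an observational design.

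The conclusion rests on four assumptions:
- the R² values in section 4.5 are population quantities;
- the protocol used the fixed-predictor formula, which is inferred from the match and not stated;
- IMR, after any transformation, is roughly normal given the covariates;
- all 50 patients are analysable. Section 5.9 expects very few losses before discharge; for illustration, 48 analysable patients would give 74.1%.

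The correlation statements and the example with base R² 0.7 need no correction.

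**What to change.** In section 4.5, name the method and replace the figure for base R² 0.3. Suggested wording: *Treating IMR and the covariates as observed, 50 patients give about 76% power for an R² gain of 0.10, or 80% power for a gain of about 0.11, when the base model R² is 0.3.*

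Optionally, add that partial correlations of 0.40 and 0.45 given the three covariates have about 81% and 90% power. This would tie the correlation figures to the model in section 6.1. They are correct as written, so the addition is not required.

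The cost is one or two sentences and a slightly less favourable stated power. No change in the number of patients is needed.
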